## Methods/Design

### Design of the study

This study is a community, parallel clinical trial, randomised by clusters, that compares two different guide implementation strategies. The intervention will be carried out on health professionals (doctors and nurses) in the PHCCs in Leganés, Madrid (Spain). The town of Leganés has nine PHCCs. for a population of 182471 inhabitants

The randomization units will be the PHCCs (clusters). The units of analysis are the mother-infant pair attended by the Leganés PHCCs. This design by clusters minimises possible contamination effects between centres. (check list cluster consort in additional file 1)

The study protocol was approved by the Area 9 Research Ethics Committee (2008/12/01), and met all good clinical practice demands.

### Subjects of the study

Mother of infants born between 1st June 2010 and 1st December 2010 who came to the PHCC on the first visit of the Child Care Programme.

#### Inclusion criteria

a. Be able to meet the demands of the trial and to be localisable for the next year, and to have the capacity to understand the questionnaires presented.

b. Give signed informed consent to be included in the study, and meet no exclusion criteria.

#### Exclusion criteria

Mothers and infants with contraindications for breastfeeding will be excluded:

a. Mothers' contraindications: HIV positive, substance abuse, chemotherapy, radioactive isotope treatments until the elimination of the isotope from the mother's body, active tuberculosis, active chickenpox, active Herpes lesions, Chagas disease.

b. Infants' contraindications: galactosemia.

### Sample size

For an alpha of 0.05, a power of 80%, and in order to detect an increase of 20% in the percentage of exclusive or preferential breastfeeding at 6 months of age in the intervention group, the overall sample size required is 176 patients (88 in each arm of the study).

Since randomisation is by clusters, the sample size has to be larger than if simple randomisation is performed, in order to take into account the design effect. The intra-class correlation coefficient is 0.01 [30] and a mean cluster size is assumed to be 30 patients. The design effect is 1.29. Given these assumptions, and expecting a 5% loss rate at one year, the final sample size required is 240 (120 patients in each arm).

### Randomisation

The randomisation unit will be the PCHC. An independent statistician will randomly assign the 9 PHCCs to either an intervention group or a control group following a simple, computer-generated random sequence (Epidat 3.1 software).

Consecutive patients will be chosen to minimise the risk of bias in their selection. During consultations, patients will be informed about the study and asked whether they would like to take part. Those who accept will be asked to give their signed consent, and checks will be made to ensure they meet all inclusion criteria but no exclusion criteria.

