## Background

### Current breastfeeding situation

The World Health Organization (WHO) considers breastfeeding the ideal way to feed infants, as it provides them with the nutrients needed for adequate growth and development, recommending exclusive breastfeeding until 6 months [1] and its continuance in supplemented form until 2 years of age [2].

Nowadays efforts are being made in both health and non-health areas for promoting the initiation and continuation of breastfeeding. Its benefits as much to the mother as to the infant, are widely known and it is thought to be an important factor in the promotion of children's health [3-6]. In spite of this, breastfeeding statistics are far from the levels considered adequate by the WHO, which estimates that 97% of women of fertile age are able to breastfeed their children.

In the latest *The State of the World's Children Report*, published in 2007 by the United Nations Children's Fund (UNICEF), it is noted that breastfeeding figures in Europe are discouraging (22% exclusive breastfeeding in infants less than 6 months old) [7]. In our country there is no official record system to make available data on the tracking and monitoring of breastfeeding. According to information from the latest *National Survey of Health*, in Spain breastfeeding at 6 months of age is 24.72% and in Madrid 23.54% [8]. In the study undertaken by the Spanish Paediatrics Association it is concluded that the average length of breastfeeding in Spain is about 3 months and only 24.8% of infants are breastfed at 6 months of age [9]. The data which has been obtained from existing records of computerised health reports in Primary Healthcare centres (PHCC) in our city show us a rather more unfavourable panorama as the percentage of 18.26%.

The WHO enumerated "*Ten Steps Towards Happy and Natural Breastfeeding" *[10] which are the basis for the introduction of projects based on the Baby Friendly Hospital Initiative (BFHI) which establishes an integrated approach to increase breastfeeding and has shown very positive results according to some studies [11,12].

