## Hypothesis

The implementation of a breastfeeding guideline, with the additional support of training and information directed at the professionals who impart the care, implies a greater integration of the guide's recommendations in usual clinical practice. As a result of this integration, an increase in the percentage of breastfed infants and a greater duration of breastfeeding will be produced.

The proportion of infants using exclusive breastfeeding (EBF) or predominant breastfeeding (PBF) at six months will increase at least 20% with respect to the control group (38% for the intervention group compared with 18% for the control group).

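### Nine PHCCs are allocated by simple randomisation with no stated split or balancing, although equal arms of 120 are planned; fixing the split at 4:5 would protect power at almost no cost

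*Protocol article*

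**What the plan says.** The Design of the study section makes the health centre the unit of allocation ("The randomization units will be the PHCCs (clusters") and gives the number available: "The town of Leganés has nine PHCCs". The Randomisation section says who allocates them: "An independent statistician will randomly assign the 9 PHCCs to either an intervention group or a control group". On the method, the same section has this done "following a simple, computer-generated random sequence (Epidat 3.1 software". Nothing in the article mentions a fixed split, blocking, stratification, matching or any constraint on the allocation.

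The Sample size section assumes equal arms: "the final sample size required is 240 (120 patients in each arm". The target in the Hypothesis section is "38% for the intervention group compared with 18% for the control group".

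The Background reports a city breastfeeding figure of 18.26%, taken from "existing records of computerised health reports in Primary Healthcare centres (PHCC) in our city". It gives no figure for any single centre.

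**The concern.** Simple randomisation, in its plain meaning, allocates each unit independently. With hundreds of patients the arms come out close to equal, but with nine centres they often do not. The sample size calculation allows for equal arms only, so an uneven split costs power that the plan has not budgeted for. In the extreme, one arm could be empty.

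All nine centres are known before allocation. The split can therefore be fixed in advance, and centre characteristics could be balanced if data on them are available. The stated method does neither.

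**Working it through.** **1. The plan's own figure.** Inputs: 18% and 38% (Hypothesis); alpha 0.05, power 80%, ICC 0.01, mean cluster size 30 and 5% loss (Sample size). Sidedness is not stated; two-sided reproduces the figure.

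- Pooled mean proportion: (0.18 + 0.38)/2 = 0.28.
- Without continuity correction: n = [1.960·√(2·0.28·0.72) + 0.842·√(0.18·0.82 + 0.38·0.62)]² / 0.20² = 77.9 per arm.
- With continuity correction: (77.9/4)·[1 + √(1 + 4/(77.9·0.20))]² = 87.6, so 88 per arm and 176 in total, as stated.
- Design effect: 1 + (30 − 1)·0.01 = 1.29, as stated.
- 176·1.29/0.95 = 239, stated as 240.

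The figure reproduces, on the basis of equal arms.

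**2. Probability of each split.** Assumption: independent allocation with probability 1/2 per centre, so the number of centres in one arm is Binomial(9, 1/2).

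- 4:5 in either direction: 2·C(9,4)/2⁹ = 252/512 = 49.2%.
- Worse than 4:5: 260/512 = 50.8%.
- 3:6: 2·84/512 = 32.8%.
- 2:7 or worse: 2·(1 + 9 + 36)/512 = 92/512 = 18.0%.
- Empty arm: 2/512 = 0.4%.

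If the program draws a fixed four or five centres, every figure except the first is zero.

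**3. Power by split.** Assumption: the 240 patients are spread evenly over nine centres, whichever arm a centre is in.

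- Analysed per centre: (240/9)·0.95 = 25.33.
- Design effect: 1 + 24.33·0.01 = 1.243.
- Effective patients per centre: 25.33/1.243 = 20.4.
- With c control and t intervention centres: SE = √[0.18·0.82/(20.4c) + 0.38·0.62/(20.4t)].
- Power from the noncentral t with 9 − 2 = 7 df (critical value 2.365, noncentrality 0.20/SE), or from the normal distribution (critical value 1.960).

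| Control / intervention | SE | Power, t on 7 df | Power, normal |
|---|---|---|---|
| 4 / 5 | 0.064 | 76% | 88% |
| 5 / 4 | 0.066 | 74% | 86% |
| 3 / 6 | 0.066 | 74% | 86% |
| 6 / 3 | 0.071 | 68% | 80% |
| 2 / 7 | 0.073 | 66% | 79% |
| 7 / 2 | 0.083 | 55% | 68% |
| 1 / 8 | 0.093 | 46% | 57% |
| 8 / 1 | 0.112 | 34% | 43% |

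Weighting the t column by the binomial probabilities, with an empty arm counted as zero power, gives an average of 70%. A fixed 4:5 split, averaged over its two directions, gives 75%. The corresponding normal-approximation averages are 82% and 87%. Using the pooled variance under the null in the normal calculation gives 85–86% at 4:5, 81–83% at 3:6 and 69–75% at 2:7, which is the same pattern.

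**4. Chance imbalance in underlying centre rates.** At the 18% control rate, ICC 0.01 implies a between-centre SD of √(0.01·0.18·0.82) = 3.8 percentage points. At 4:5 the chance difference between arms then has SD 3.8·√(1/4 + 1/5) = 2.6 points, against a target difference of 20 points.

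**5. How far a constraint can go.** There are C(9,4) + C(9,5) = 252 allocations with a 4:5 split, counting both directions. Keeping about 10% leaves 25. If the kept set is symmetric, so that each allocation's mirror image is also kept, the smallest two-sided permutation p-value is 2/25 = 0.08. To fall below the plan's 0.05 level, more than 2/0.05 = 40 allocations must be kept.

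**The case against.** Four points can be made for the plan, and each stands in part.

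- **The wording does not settle how the split arises.** A computer-generated random ordering of nine centres, cut after four or five, could be described in the same words and would fit the planned equal arms. A reader might infer that the trial simply has a 51% chance of a poor split. The article does not support that without the condition of independent allocation.
- **Most of the gap below 80% is not due to the split.** The 7-df reference already gives only about 75% at 4:5. The Statistical Analysis section names a chi-squared test and a random-effects logistic model, not this t-test. The small number of clusters is a separate limit that no allocation scheme removes. The 3:6 split with more intervention centres (74%) matches the lower 4:5 figure, and on the normal approximation 3:6 still reaches the 80% target in either direction.
- **Serious baseline imbalance is not shown.** It is tempting to say that with nine centres it is likely. Under the protocol's ICC the SD of the arm difference is only 2.6 points, and the design effect already allows for that variation. An assumed ICC of 0.05 would give √(0.05·0.18·0.82)·√(1/4 + 1/5) = 5.8 points, but nothing in the article points to that value. No variation in centre size is reported either.
- **Rates per centre are an inference.** The Background gives one pooled figure from the centre records. It does not say whether rates by centre can be extracted, how complete they are, or whether they match the trial's endpoint.

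The planned baseline comparison and covariate adjustment help with maternal factors. They do not restore power lost to an uneven split.

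**Conclusion.** The point holds as one of efficiency. The article names simple randomisation for nine units, states no split, and plans equal arms. If allocation is independent, there is a 51% chance of a split worse than 4:5 and an 18% chance of 2:7 or worse. The average cost is about 5 percentage points of power (75% to 70% on 7 df). The loss is small at many 3:6 outcomes and material mainly at 2:7 or worse, where power is 66% or less on 7 df and 79% or less on the normal approximation.

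These figures rest on independent allocation, 240 patients spread evenly over the centres, ICC 0.01 and 5% loss. If the software fixed four or five centres, the split part disappears and only the absence of balancing on centre characteristics remains, with an effect that the article's figures suggest is modest.

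A reader might conclude that the allocation is biased. It is not: simple randomisation of clusters is valid, and what is lost is precision.

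**What to change.** **If allocation has not been drawn:** use restricted randomisation of the nine PHCCs with the split fixed at 4:5, and say so in the Randomisation section. Where centre data can be extracted from the existing records, also stratify or lightly constrain on PHCC size and pre-trial breastfeeding rate. Set in advance a minimum number of the 252 allocations to keep. A symmetric set of about 25 is too small for a permutation test at 0.05. Reflect the balancing variables in the analysis.

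**If allocation has been drawn**, which is possible because the Subjects section describes births in June to December 2010 partly in the past tense: report the actual split and how it was generated, restate the power for it, and prespecify adjustment for each PHCC's pre-trial rate if that rate is available.

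**Cost:** a little of the independent statistician's time, plus the extraction of centre rates if they are used. No additional patients are needed.

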### Masking

In a study of this type it is impossible to mask the intervention. The analysis data will be performed by independent professionals blinded to the assignment group.

### Intervention

#### Control group (usual diffusion)

Presentation of the Breastfeeding Guideline in a one-off centralised clinical session for all PHCCs, 60 minutes in length. Two members of each of the 9 PHCCs will be invited to attend.

The Breastfeeding Guideline will be made available on the PHCC's webpage.

#### Intervention group

As well as the usual diffusion, the following implementation strategy will be carried out in each PHCC:

Training: three training sessions of one and a half hours in length will take place for all the health professionals. These will be given in the PHCC by the investigators.

Responsible person/opinion leader: a professional responsible for breastfeeding in each PHCC will be appointed (doctor, nurse, midwife or social worker).

### Variables

#### Outcome variables

The main outcome variable is the mother-infant pairs using EBF o PBF at six months

The secondary outcome variables will be:

##### Professional variables

Socio-demographic: sex, age, number of children.

Professional profile: paediatrician/midwife/nurse/nursing assistant/family doctor/medical intern (family/paediatrician). Years of professional experience. Breastfeeding training received and level of breastfeeding knowledge measured by means of Temboury's questionnaire [15].

##### Mother-infant pair variables

Mother: age, nationality, member of a stable couple, educational level (low - primary studies only; medium - high school completed, technical training or other non-university studies completed; high - university level education completed). Working situation of the mother: if she works outside the home and the number of hours per working day/days per week.

Prior information: If she has received breastfeeding information during her pregnancy and if she has attended prenatal training sessions.

Previous pregnancies: if affirmative, her pregnancy history will be recorded.

Previous breastfeeding experience (details for each child): length and type of breastfeeding for previous children; exclusive/preferential/partial. Reason for ceasing breastfeeding: mother's decision/no weight-gain/contraindication because of mother's illness (state which)/contraindication because of child's illness (state which)/contraindication with medications/nipple problems/other technical difficulty.

Current pregnancy: Birth date and type of birth: vaginal/caesarean; single/multiple. Gestational age of child in weeks, birth-weight in grams. Breastfed: a) if yes: EBF or PBF; b) if not: date of ceasing breastfeeding and the reason for abandoning breastfeeding.

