## Objectives

The aim of the present work is to determine whether an implementation strategy for a breastfeeding guide is more effective than the usual diffusion in terms of increasing the percentage of infants using EBF or PBF at 6 months.

Secondary objectives:

To determine whether an implementation strategy for a breastfeeding guide is more effective than the usual diffusion in terms of increasing the percentage of infants using EBF or PBF at 1, 3 and 12 months.

To determine whether an implementation strategy for a breastfeeding guide is more effective than the usual diffusion on duration of EBF and PBF.

To evaluate knowledge on breastfeeding possessed by health professionals prior to undertaking the intervention.

Describe the reasons for withdrawal from breastfeeding in both groups.

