### Data collection method

a) From professionals: the collection of socio-demographic data on the health professionals and the completion of the questionnaire on breastfeeding knowledge will take place before the start of any other activity.

b) From mothers: The inclusion of mothers in the study will take place on the infant's first consultation at the PHCC. The nurse and/or paediatrician will inform the mother and request her consent.

The collection of information about the breastfeeding will be by telephone interview, undertaken by an individual interviewer trained for the purpose; who does not know to which group the woman belongs.

Phonecalls will be scheduled at 1, 3, 6 and 12 months from the beginning of the study. During each call the mother will be asked if the infant is being breastfed at that time and, if the answer is negative, will be asked the date breastfeeding ceased and the reason for stopping. Each woman will be followed for a period of 12 months from the child's birth or until the time when breastfeeding ceases.

The timing of collection of data on the different variables is shown in Figure 1, in which the project structure and the data collection procedure are shown.

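### As written, the feeding record has no code for partial breastfeeding and dates only the end of all breastfeeding, so duration of exclusive and predominant breastfeeding cannot be properly analysed

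*Protocol article*

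**What the plan says.** The primary endpoint (Outcome variables) is binary: "The main outcome variable is the mother-infant pairs using EBF o PBF at six months". A secondary objective (Objectives) asks whether the strategy is "more effective than the usual diffusion on duration of EBF and PBF". The Statistical Analysis section assigns that objective to a log-rank comparison, with Cox models for confounding, by type of breastfeeding.

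The data meant to feed these analyses are described in two places. Under Mother-infant pair variables, the current infant's feeding is "Breastfed: a) if yes: EBF or PBF; b) if not: date of ceasing breastfeeding and the reason for abandoning breastfeeding". Under Data collection method, the call works the same way: "During each call the mother will be asked if the infant is being breastfed at that time". Only a mother who says no is then asked when and why breastfeeding stopped; a mother who says yes gives no date. The calls are timed thus: "Phonecalls will be scheduled at 1, 3, 6 and 12 months from the beginning of the study". Follow-up of each woman ends at 12 months from birth or when breastfeeding stops.

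For earlier children, the same variable list records "length and type of breastfeeding for previous children; exclusive/preferential/partial".

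**The concern.** Partial breastfeeding is a state the authors recognise, since they record it for earlier children. It is absent from the options for the child who carries the endpoint. The Background also describes continued supplemented breastfeeding after 6 months as the WHO recommendation, so the missing state is one the trial should expect to meet, above all at the 12-month call.

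Two things are at stake. First, duration of EBF and of PBF needs the date on which each ended, and the stated rule collects a different date. Second, if interviewers fit partial feeders into the available options, the 6-month outcome drifts from EBF/PBF towards any breastfeeding. Neither loss can be reliably repaired once the calls have been made.

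**Working it through.** **1. Route of an infant through the stated rule.** Take an infant on EBF who starts formula between the 1 and 3 month calls and stops the breast altogether between the 6 and 12 month calls.

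| Call | True state | Answer to the call question | Type offered | Date taken |
|---|---|---|---|---|
| 1 month | exclusive | yes | EBF fits | none |
| 3 months | partial | yes | neither fits | none |
| 6 months | partial | yes | neither fits | none |
| 12 months | none | no | not applicable | end of all breastfeeding |

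The only date on file is the end of all breastfeeding. The end of EBF, which came at least 3 months earlier (before the 3-month call rather than after the 6-month call), has no date. A move from EBF to PBF is undated for the same reason: the mother answers yes and no date is asked.

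**2. What could still be recovered for duration.** If type is recorded correctly at each call and left blank for partial feeders, the end of EBF/PBF falls in one of the brackets 0-1, 1-3, 3-6 or 6-12 months, that is 1, 2, 3 or 6 months wide. (This takes the calls as timed approximately from birth.) A log-rank test or Cox model on single event times would have to use either an arbitrary point in the bracket or the recorded cessation date. The latter is any-breastfeeding duration.

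**3. What could still be recovered for the primary outcome.** A breastfed infant marked neither EBF nor PBF at 6 months can be counted as a non-success, which is correct. Misclassification arises only if the interviewer selects EBF or PBF for that infant (false success) or enters the infant as stopped. The latter gives the right binary result but needs a cessation date that does not exist.

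**4. Plan's own sample size.** Inputs (Hypothesis and Sample size): 18% v 38%, alpha 0.05 (taken as two-sided), power 80%, intra-class correlation 0.01, cluster size 30, loss 5%.
- Two proportions: 78 per arm uncorrected and 88 with continuity correction, so 176 in total, as stated.
- Design effect: 1 + (30 - 1) x 0.01 = 1.29, as stated.
- Final size: 176 x 1.29 / 0.95 = 239.0, against the stated 240.

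The sample size reproduces and this point does not touch it.

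**5. Illustration for the primary outcome.** The document gives no partial-feeding rate, so every share below is an assumption, and every partial feeder is taken to be coded as a success. Effective n per arm = 120 x 0.95 / 1.29 = 88.4. Power = Phi{[d x sqrt(n) - 1.96 x sqrt(2 x pbar x (1 - pbar))] / sqrt[p1(1 - p1) + p2(1 - p2)]}, where d = p2 - p1 and pbar = (p1 + p2)/2, without continuity correction.
- No partial feeders, 18% v 38%: power 0.85.
- Equal partial share in both arms of 5%, 10%, 20% or 30%: the difference stays at 20 points; power 0.81, 0.79, 0.76 or 0.77.
- 20% partial in control, with 25%, 50% or 100% of the 20-point gain coming from partial feeders who move to EBF/PBF: recorded rates 38% v 53%, 48% or 38%; recorded difference 15, 10 or 0 points; power 0.52, 0.27 or 0.025 (upper tail only).

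The effect on the primary outcome therefore runs from small to complete. It depends on the partial share, how partial feeders are coded and where the gain comes from, none of which the document settles.

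**The case against.** The strongest reply is that a journal article condenses the forms. The questionnaire and the figure on data collection are not shown, the interviewer is trained for the task, and the team plainly knows the three-way classification. The single line on the current infant may be abbreviated drafting. This limits what can be said about the actual forms. It does not remove the point, because the article is not silent: it states the response options and the rule for taking a date, and these do not deliver its own duration objective.

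A reader might go further and infer that the primary outcome cannot be obtained either. The text does not support that. Type is recorded under the yes branch and the endpoint is binary, so an untyped breastfed infant can be counted as a non-success.

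A reader might also infer a large bias by adding an assumed 10-25% of partial feeders to the 18% control rate, giving 28-43%, and setting that shift beside the 20-point effect. That compares a shift in the control level with a between-arm difference, and equal misclassification leaves the difference unchanged. The assumed share has no source in the document.

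Nor is it certain that the duration analysis would end up as any breastfeeding, since types recorded at the calls could bracket the change. That part of the reply stands: it is a risk, and bracketing is a coarse substitute.

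**Conclusion.** Wrong as written, mainly for the secondary objective on duration. Under the stated rule, any mother who moves from EBF or PBF to partial feeding has no recorded end date for EBF/PBF. The planned log-rank and Cox analyses then rest on brackets of 1 to 6 months or on the wrong event.

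The 6-month primary outcome is exposed to misclassification but recoverable. The power figures above only illustrate how far the answer depends on unknown shares, and no size of bias can be claimed from the document. The conclusion assumes that the response options and the call rule are applied as the article states them. If the unseen forms already hold a partial category and separate end dates, the remedy reduces to correcting the article.

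**What to change.** - At every call, record current feeding as exclusive, predominant, partial or none. Count only exclusive or predominant as success at 1, 3, 6 and 12 months.
- Ask the date on which EBF ended, the date on which PBF ended and, as now, the date on which all breastfeeding ended. A single date for the first other food or milk would not be enough, because it does not separate EBF from PBF.
- Use the EBF and PBF dates as the events in their respective survival analyses, and report any-breastfeeding duration separately.
- Align the wording under Mother-infant pair variables and Data collection method with these rules.

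The cost is one extra response category and short date questions in calls already scheduled. The dates will carry some recall error, most in the longer gaps between calls.
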